**8.2. Evaluate the adverse event**

Mild: No need for therapeutic intervention.

Severe: Immediate need for therapeutic intervention.

**8.3. Expected adverse events**

Blood stasis, swelling, ischemia, skin discoloration, numbness, and ache of the finger at the cuff attachment site of the ClearSight.

**8.4. Countermeasures for serious adverse events**

Not applicable

**8.5. Compensation for health damage**

Not applicable

**9. Observation, inspection, report items and schedule**

**9.1. Participation period of subjects**

Start of research study period: Time data collection begins after induction of the general anesthesia.

End of research study period: 4 hours after admission to the ICU or 24 hours after the start of the study period, whichever comes first.

**9.2. Observations, inspection, and information to report**

**9.2.1 Characteristics of subjects**

Height, weight, sex, American Society of Anesthesiologists (ASA) physical status, co-morbidity, and medical history.

**9.2.2 Perioperative data**

An arterial catheter is inserted into the left radial artery of each patient after the induction of general anesthesia. The finger cuff of the ClearSight system is placed over the left middle phalanx of the third finger, ipsilateral to the radial artery catheter. The pulse oximeter probe is attached to an ipsilateral finger not competing with the finger cuff of the ClearSight.

**ClearSight:**

Systolic arterial pressure (SAPcs), diastolic arterial pressure (DAPcs), mean arterial pressure (MAPcs), CO, SV, and SVV data are recorded at 20-second intervals.

**FloTrac (arterial catheter):**

SAP, DAP, MAP, CO, SV, and SVI data are recorded at 20-second intervals.

**Radical-7 pulse oximeter:**

PI and SpO_2_ data are recorded at 10-second intervals.

**Anesthetic monitor in the operating room and in the ICU:**

Heart rate, body temperature, and central venous pressure data are recorded in 1-minute intervals.

**Fast-flush test (square wave test):** Performed by the anesthesiologists both in the operating room and in the ICU and documented by filling-in the recording sheet.

**9.2.3 Other information to record**

**Time information:** anesthesia time, each measuring period, starting time of the operation, time of the specimen extraction, time of the intestinal anastomosis, and finishing time of the operation.

**The artifact of the IAP due to body movement or blood sampling**

**The information of the vasopressors**

These data are documented on the recording sheet by anesthesiologists in the operating room and the ICU, or nurses in the ICU.

**9.3. Measuring schedule**

One measurement period is defined as 15 minutes. In the operating room, anesthesiologists who are not involved in the data analysis plan for a two-hour operation that will result in at least 8 measurement periods from skin incision until skin suture when the hemodynamic condition is relatively stable. One hundred twenty data pairs will be obtained from one subject in the operating room. In the ICU, at least 2 measurement periods are planned per subject until 4 hours after arrival in the ICU, so that the total number of measurement periods per subject will be at least 10. We plan on obtaining 150 data points per subject, at least. However, these are just target numbers. It is possible to increase or decrease the measurement periods depending on the actual operation situation or the time of admission to the ICU.

**10. Definition of the endpoints**

**10.1 Primary endpoint**

The standard deviation (SD) of the bias between arterial pressures measured with the ClearSight versus those measured with an arterial catheter.

**10.2 Secondary endpoint**

(1) The beta coefficient of the bias using the linear mixed-effects model between arterial pressures measured with the ClearSight versus those measured with an arterial catheter.

(2) The percentage error of the arterial pressure.

(3) Interclass correlation coefficients of the arterial pressure.

(4) The beta coefficient of the CO, SV, and SVV calculated by the linear mixed-effects regression model.

**11. Statistical analysis**

**11.1 Sample size**

**Estimated sample size before starting the recruitment: 30 cases**

**Grounds:** First, the cut-off value of the PI is defined as 1 (described in the pulse oximeter manual as a measure of hypoperfusion and clinical acceptability). Second, it is assumed that the acquirable number of data points of the PI ≤ 1 and those points of the PI > 1 are equal. The bias of the arterial blood pressures between the two devices is assumed to be 8.4 mm Hg based on a past study.[9] The total number of data points is determined to detect a 1.35-fold difference in the ratio of the SD of the bias between those with a PI ≤1 and >1. Assuming that at least 10 measurement periods can be secured per subject, the sample size is calculated by an *F*-test to be 25 with an *α* error of 0.05 and a 1–*β* of 0.9. We are planning for a sample size of 30 cases in anticipation of possible dropout. According to the Association for the Advancement of Medical Instrumentation (AAMI) SP10.2002, a minimum of 15 subjects and 10 readings per subject should be reported for the proof of accuracy for noninvasive blood pressure (NIBP) devices. This criterion has been applied in the past in similar studies about the accuracy of the noninvasive arterial pressure monitor.[10] In comparison to the above, our sample size is considered to be roughly reasonable. The measurement period should be set as evenly as possible during the operation.

**11.2. Analysis sets**

Statistical analysis is performed using all cases for which the data collection is properly performed.

**11.3. Methods and items**

**11.3.1** **Analysis of the primary outcome**

**Linear mixed-effects regression model**

**(calculating the SD of the bias between the two devices)**

Response variable: The mean differences between the two devices.

Covariate: Binarized PI (PI ≤1 and PI >1), heart rate, body temperature, and the mean values of the APcs and the IAP.

Random effect: Subject

The model allows the variances of the bias to differ depending on the binarized PI.

Based on the results of this model, the ratio of the adjusted SD of bias is calculated.

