**Analysis of the primary outcome**

Linear mixed-effects regression model (calculating the SD of the bias between the two devices)

Response variable: The mean differences between the two devices.

Covariate: Binarized PI (PI ≤1 and PI >1), heart rate, body temperature, the mean value of arterial pressure measured by the ClearSight (APcs), and the invasive arterial pressure.

Random effect: Subject

The model allows the variance of the bias to differ depending on the binarized PI.

Based on the results of this model, the ratio of the adjusted SD of bias is calculated.

If the PI value is determined to be an indicator of the agreement of the ClearSight and the invasive arterial pressure, it may be possible to judge the reliability of the APcs value in real time. Our study may beneficially contribute to patients by providing a minimally invasive solution.

0.6. **Lead principal investigator**

[name], Department of Anesthesiology and Critical Care Medicine, Yokohama City University Hospital

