**1. Object and meaning**

ClearSight™ (Edwards Lifesciences Corporation, Irvine, CA USA) is a noninvasive monitor for measuring the arterial blood pressure, cardiac output (CO), or the other hemodynamic parameters such as stroke volume index (SVI), stroke volume variation (SVV), or systemic vascular resistance index (SVRI). With widespread use of the ClearSight, healthcare providers will be able to provide care in a less invasive manner.

The agreement between the arterial pressure values measured by the ClearSight (APcs) and the arterial catheter-based blood pressures (IAP) has been examined by several studies.[1-4] In patients undergoing cardiac surgery or those in the intensive care unit (ICU) after cardiac surgery, the APcs shows sufficiently good bias and precision to substitute for IAP. However, APcs is not reliable in critically ill patients or in those receiving vasopressors to maintain their blood pressure.[5-7] It has been speculated that the unreliability may be due to reduced finger perfusion from high peripheral vascular resistance, continuous vasopressor administration, and/or edema, but the evidence is lacking.

We hypothesized that lower peripheral perfusion would affect the agreement between the arterial APcs and the IAP. As an indicator of peripheral perfusion, we chose the perfusion index (PI) measured by pulse oximetry, which is calculated as the ratio of the pulsatile infrared signal to the non-pulsatile infrared signal in the peripheral tissue.[8] The PI can be obtained continuously and noninvasively, and lower values indicate peripheral hypoperfusion or vasoconstriction.

The primary objective of this study is to assess whether the PI affects the agreement between APcs and IAP. The secondary objective of this study is to assess whether the PI affects the agreement between cardiac output, SVI, SVV, or SVRI as measured by the ClearSight and those measured by the FloTrac system (Edwards Lifesciences Corporation, Irvine, CA USA). If the PI value is determined to be an indicator of the agreement of the ClearSight and the invasive arterial pressure, it may be possible to judge the reliability of the APcs value in real time. Our study may beneficially contribute to patients by providing a minimally invasive solution.

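### The primary model gives all subjects the same error SD within a PI class, so the model-based uncertainty of the SD ratio is too narrow if patients differ in both ClearSight scatter and PI share

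*Protocol*

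**What the plan says.** Section 10.1 makes the scatter of the device difference the primary endpoint: "The standard deviation (SD) of the bias between arterial pressures measured with the ClearSight versus those measured with an arterial catheter". Section 11.3.1 analyses it with a linear mixed model whose only random term is "Random effect: Subject". On the error variance it says "The model allows the variances of the bias to differ depending on the binarized PI", and section 0.5 says the same. The result is then defined: "Based on the results of this model, the ratio of the adjusted SD of bias is calculated". Neither section names a test, standard error or interval for that ratio, a variance term for subject, or resampling by subject.

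The inferential frame comes from section 11.1. The design is meant to "detect a 1.35-fold difference in the ratio of the SD of the bias", and "the sample size is calculated by an *F*-test to be 25 with an *α* error of 0.05 and a 1–*β* of 0.9". That calculation counts 10 measurement periods per subject and assumes equal numbers of points in the two PI classes overall. It does not say how they divide within a patient. Section 9.3 plans at least 150 data points per subject, and section 7.1 makes each one a one-minute average.

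**The concern.** A subject random effect on the mean absorbs patients whose ClearSight reads consistently high or low. It does nothing for patients whose readings are consistently noisier. Under the stated model, each PI class has one SD shared by all 25 to 30 patients, and the precision of the ratio is driven by the number of minutes.

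If patients differ in scatter, and also in how much of their time falls at PI ≤1, each patient's own SD weighs unequally on the two classes. By chance, noisier patients may fall mostly on one side of the PI cut. The ratio then moves away from 1, in either direction, although PI does nothing, and the model's standard error does not allow for it. What is at stake is a claim that PI indicates agreement, which section 1 would use to judge reliability in real time. The mechanism operates with fully independent minutes, so it is separate from serial correlation.

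**Working it through.** **1. The plan's own figure.** For a two-sided comparison of two SDs with equal groups, n per class ≈ 1 + [(1.960 + 1.282) / ln 1.35]² = 1 + (3.242 / 0.3001)² ≈ 118. The exact *F*-test needs 119, so 238 points, or 23.8 subjects at 10 each. The stated 25 subjects give 125 per class and power 0.914. The arithmetic of section 11.1 therefore reproduces. Its premise is independent points with one common SD per class.

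**2. Inputs.** From the protocol: N = 25 subjects, m = 150 values (section 9.3) or m = 10 (section 11.1), equal PI classes overall, ratio 1.35. The 8.4 mm Hg cancels in a ratio.

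Assumed, because the protocol gives no figure:
- τ, the between-patient SD of the log error SD: 0, 0.1, 0.2 or 0.3. At 0.3, a patient one SD above the median has exp(0.3) = 1.35 times the median scatter.
- The share p of a patient's values at PI ≤1: Beta(2,2), variance 0.05, or uniform, variance 1/12.

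Values are independent within patient. The heart rate, temperature and pressure covariates are left out.

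**3. Formulae.** The model's variance of the log SD ratio is V_model = 1/(2n₀) + 1/(2n₁) = 2/(Nm):
- m = 150: 2/3750 = 0.000533, SE 0.0231.
- m = 10: 2/250 = 0.008, SE 0.0894.

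The pooled variances of the two classes weight patient i's variance by p and 1 − p. The difference in weight is about (2/N)(2p − 1). With k = exp(4τ²) − 1 (the squared CV of the patient variances) and v = Var(p) + E[p(1 − p)]/m, the actual variance is about

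V_true ≈ 4vk/N + (1 + k)·V_model, and rejection ≈ 2[1 − Φ(1.96·√(V_model/V_true))].

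Example, τ = 0.3, Beta(2,2), m = 150:
- k = exp(0.36) − 1 = 0.433 and v = 0.05 + 0.20/150 = 0.0513.
- V_true = 4 × 0.0513 × 0.433/25 + 1.433 × 0.000533 = 0.00356 + 0.00076 = 0.0043, so the SD is 0.066 against a model SE of 0.023.
- Rejection ≈ 2[1 − Φ(0.69)] = 49%.

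**4. Rejection of a true ratio of 1, nominal 5%** (Beta(2,2) to uniform)

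| τ | 150 values: formula | 150 values: simulated | 10 values: formula | 10 values: simulated |
|---|---|---|---|---|
| 0.1 | 13-17% | 12-18% | 6% | 6-7% |
| 0.2 | 32-41% | 30-38% | 10-11% | 10% |
| 0.3 | 49-58% | 45-53% | 17-20% | 16-20% |

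With τ = 0, simulated rejection is near 5%. If every patient is split exactly 50/50 by PI, it is 5-9% at 150 values for τ of 0.2 to 0.3. The median estimated ratio is 1.00. At τ = 0.3, Beta(2,2) and 150 values, 95% of null estimates lie between 0.88 and 1.13.

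**5. Subject-level inference.** A leave-one-subject-out jackknife on the same pooled ratio brings rejection to 4-5% in one set of simulations and about 7.5-8.3% in another. Power for 1.35 at τ = 0.3 is roughly Φ(0.300/√V_true − 2.064):
- 150 values: 0.300/0.0658 − 2.064 = 2.50 gives 99% (Beta(2,2)); 0.300/0.0814 − 2.064 = 1.62 gives 95% (uniform). Simulation gives 93-97%.
- 10 values: 0.300/0.1277 − 2.064 = 0.29 gives 61%; 0.300/0.1356 − 2.064 = 0.15 gives 56%. Simulation gives about 50-55%.

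**The case against.** The strongest reply is that section 11.3.1 only calculates a ratio. It names no test or interval, so a separate analysis plan could attach cluster-robust uncertainty to the same model. This stands in part: the test examined here is inferred from the *F*-test, the 0.05 and the 1.35 of section 11.1. But the protocol does fix the variance structure, and the error bars that come with that model carry the fault.

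Second, both drivers are assumed. Recording edema and hypertension history does not show that scatter differs by patient, and section 1 mentions edema as a route through finger perfusion, that is, through PI. Some of the design favours PI changing within a patient: section 2.1 expects intraoperative vasoconstriction, and periods are spread over the operation and into the ICU. This stands, and is why the size is given as a range.

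Third, 150 consecutive minutes are not independent, and on the 10-value sizing basis the inflation is much smaller. That is true for an analysis at period level. Section 7.1, however, makes each minute a datum, and the stated model has no term for period.

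Fourth, no section demands a within-patient ratio, and the pooled SD at a given PI in a new patient is a legitimate target. This also stands, so the pooled ratio can remain primary.

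**Conclusion.** The point holds as a conditional one. Followed as written, the model leaves patient-to-patient differences in scatter out of the uncertainty of the primary ratio. With modest spread the effect is material at the planned data density (about 30-38% rejection at τ = 0.2 with 150 independent values) and small to moderate at 10 values (about 10%). It vanishes without spread and nearly vanishes with an even PI split in every patient.

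A reader might infer more: that the model biases the ratio, or that a true null will certainly be rejected far too often. The documents do not support either. The estimate is over-dispersed and not shifted, no test is named, and neither the spread of scatter nor the clustering of PI is given. Nor does the protocol's hypothesis ("We hypothesized that lower peripheral perfusion would affect the agreement between the arterial APcs and the IAP") require the pooled model to be abandoned for a within-patient one. The mechanism is firm; its size in this trial is unknown.

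**What to change.** In sections 11.3.1 and 0.5, keep the pooled SD ratio and state that its confidence interval and test come from resampling whole subjects (bootstrap or jackknife). Add as a sensitivity analysis a model with a subject-specific residual SD and a common PI ratio, which isolates the within-patient effect that real-time use relies on.

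No new data are needed. The cost is wider intervals. At τ = 0.3, power for 1.35 with subject-level inference is about 93-97% with 150 independent values but only some 50-60% with 10 (simulation and formula together), so the 90% in section 11.1 should be re-checked and restated on this basis. The sensitivity model draws nothing from patients whose PI never crosses 1. At 10 values and τ = 0.3 its simulated power was 61% with Beta(2,2) shares and 32% with the more polarised Beta(0.5,0.5), so it should not be presented as confirmatory without its own power check.

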**Anesthetic monitor in the operating room and the ICU:**

Heart rate, body temperature, and central venous pressure data are recorded at 1-minute intervals.

The systolic, diastolic, and mean arterial pressures, and the CO, SV, and SVI data obtained using the ClearSight and the FloTrac are recorded at 20-second intervals, and a set of three consecutive data points (obtained over 1 minute) are averaged to yield one datum. The IAP, heart rate, and body temperature are recorded at 1-minute intervals and stored on an anesthesia monitor. PI values are recorded and stored at 10-second intervals on the pulse oximeter. The representative value of PI data obtained every minute are calculated by averaging six consecutive PI values. No manual description of measured values is required, because these data are automatically stored in these measuring devices.

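### The primary model treats about 150 one-minute values per subject as independent given a subject intercept, so a model-based interval or test for the SD ratio can be too narrow

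*Protocol*

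**What the plan says.** **Model.** Protocol 11.3.1 (also outline section 0.5) models the device difference on binarized PI, heart rate, temperature and mean pressure. The only grouping term is "Random effect: Subject". On the residuals it says: "The model allows the variances of the bias to differ depending on the binarized PI". The ratio of adjusted SDs is then to be calculated, and no interval or test is named. This SD is the primary endpoint (10.1). Secondary endpoint (1) in 10.2, the bias coefficient, comes from the same model (11.3.2).

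**Data.** Section 7.1 states that "a set of three consecutive data points (obtained over 1 minute) are averaged to yield one datum". Section 9.3 sets 15-minute periods, at least 10 per subject, and says: "We plan on obtaining 150 data points per subject, at least".

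**Sample size.** Section 11.1 uses an F-test to "detect a 1.35-fold difference in the ratio of the SD of the bias between those with a PI ≤1 and >1". It assumes an equal split of data points between the PI classes and continues: "Assuming that at least 10 measurement periods can be secured per subject". The result is 25 subjects, raised to 30 for dropout.

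**The concern.** A subject intercept absorbs a constant offset between the devices within a patient. It does not absorb minute-to-minute persistence of the difference, shifts between periods, or patients whose differences scatter more than others'. The residual SD is the primary quantity, so whatever the residual structure leaves out bears directly on the precision claimed for the primary result.

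The protocol gives reasons to expect such dependence. Periods are placed when haemodynamics are relatively stable (9.3), which favours a steady PI class within a period. Transducer damping is rechecked before each period and the cuff may change finger (7.1, 7.2). Periods span the operating room and the ICU.

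At stake is the false-positive rate for the main claim, that PI signals in real time when the noninvasive pressure is unreliable. Sections 11.1 and 11.3.1 also imply very different amounts of information per subject.

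**Working it through.** **1. The plan's own figure.** Inputs from 11.1: SD ratio 1.35 (variance ratio 1.35²), equal groups, alpha 0.05, power 0.90. The exact two-sided F-test needs 119 points per PI class, 238 in all. At 10 per subject, 238/10 = 23.8, so 24 subjects against 25 stated; 250 points give power 0.914. The one-sided test needs 194 points (20 subjects) and does not reproduce 25. At 150 independent points per subject, 238/150 = 1.6, so about 2 subjects would do.

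**2. Precision implied by each unit.** For independent values, SE(log SD ratio) = √(1/(2n₁) + 1/(2n₂)).
- 10 per subject, 25 subjects, n₁ = n₂ = 125: √(2/250) = 0.089; 95% interval factor exp(1.96 × 0.089) = 1.19.
- 150 per subject, n₁ = n₂ = 1,875: √(2/3,750) = 0.023; factor 1.05.

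The planning unit gives an SE √15 = 3.9 times that of the analysis unit.

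**3. Serial correlation (assumed AR(1), lag-1 correlation ρ; PI class constant within a period).** The variance inflation is D = 1 + 2 Σₖ₌₁¹⁴ (1 − k/15) ρ²ᵏ, the true SE is 0.0231 × √D, and the type I error is 2[1 − Φ(1.96/√D)].

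| ρ | D | √D | true SE | type I error |
|---|---|---|---|---|
| 0.3 | 1.18 | 1.09 | 0.025 | 7% |
| 0.5 | 1.61 | 1.27 | 0.029 | 12% |
| 0.7 | 2.67 | 1.63 | 0.038 | 23% |
| 0.8 | 3.90 | 1.97 | 0.046 | 32% |
| 0.9 | 6.66 | 2.58 | 0.060 | 45% |
| 0.95 | 9.57 | 3.09 | 0.071 | 53% |

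**4. Simulation of the written model.** 25 subjects × 10 periods × 15 minutes, true ratio 1, subject intercept plus two residual variances. Covariates other than PI were omitted.
- PI constant within a period: 11% at ρ = 0.5, 24% at 0.7, 31–35% at 0.8, 50–52% at 0.9. Independent residuals gave 3–7%, which is 5% within simulation error.
- PI class switching at random each minute, ρ = 0.9: 5%, with empirical and model SE both 0.023.
- Intermediate persistence (latent PI itself AR(1) at 0.9; intercept removed by centring): 9%, 16%, 21% and 32% at residual ρ of 0.5, 0.7, 0.8 and 0.9.
- Residual SD differing between subjects, no serial correlation: at SD of log-SD 0.2, from 14% to 41% depending on how far PI differs between subjects. At 0.3, 37% with PI mixed within subjects and 71% with PI mostly fixed per subject (empirical SE 0.112, model SE 0.023).
- ρ = 0.9 plus heterogeneity of 0.2–0.3: 54–72%.
- PI coefficient (Wald test) in scenarios with correlated residuals: 47–58%, against 7% with independent residuals.

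**5. Remedy.** A leave-one-subject-out jackknife of the model's own SD ratio held 3–5%.

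**6. Power for 1.35.** log 1.35 = 0.300. At ρ = 0.95, Φ(0.300/0.0714 − 1.96) = 0.987; it is higher at every smaller ρ.

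**The case against.** Four objections carry weight.

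- **No inference is named.** Section 11.3.1 says only that the ratio is calculated. A reader might infer that the protocol prescribes a likelihood-ratio or Wald test; it does not. An interval method could stand in an analysis plan that is not at hand. This makes the point conditional but does not remove it: the protocol fixes the random effect and the variance structure, and any interval taken from that model inherits them.
- **The size rests on assumptions.** A reader might infer that the intervals are certainly far too narrow. The documents give no autocorrelation, PI persistence or between-subject SD. With PI switching at random each minute, serial correlation does no harm, and at ρ = 0.3 the SE is short by only 9%. The omitted covariates might also absorb some slow drift. The values are independent only conditionally on the subject intercept, so the model does not ignore clustering altogether.
- **The practical harm is limited.** At ρ = 0.9 the empirical SE of 0.068 puts the null ratio mostly within exp(±1.96 × 0.068) = 0.88 to 1.14, well short of 1.35. The main risk from serial correlation is that small ratios are called significant.
- **Ten units per subject may be a deliberate allowance for correlation.** If so, 11.3.1 should carry the same allowance, and it does not.

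A period effect with AR(1) residuals may look like the natural remedy. Alone it is not: it leaves differences in residual SD between subjects untouched, and it moves between-period variation out of the SD that defines the endpoint.

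**Conclusion.** The concern holds conditionally. As written, the model treats about 150 one-minute values per subject as independent given the subject intercept, while the sample size credits each subject with 10. A model-based interval or test for the SD ratio is too narrow if PI class persists within periods or subjects, and either the differences are serially correlated or residual SD varies between subjects.

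With strong persistence, type I error at a nominal 5% is about 11–12% at ρ = 0.5, 23–35% at 0.7–0.8, and roughly 40–70% at 0.9 or with SD heterogeneity. Weaker persistence gives lower figures, down to 5%. The PI coefficient in secondary endpoint (1) is exposed in the same way.

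The documents do not support a claim that the estimated ratio is biased or that serial correlation leaves the trial underpowered for 1.35: power was at least 0.98 for every AR(1) value tried. That figure does not cover the most adverse heterogeneity case, where the SE of 0.112 exceeds the planning value of 0.089.

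**What to change.** In 11.3.1, keep the model and its SD-ratio estimate. State that the interval and test for the ratio, and for the PI coefficient in secondary endpoint (1), come from resampling whole subjects. This can be a cluster bootstrap, or a leave-one-subject-out jackknife with t on the number of subjects minus 1 degrees of freedom. State the same analysis unit in 11.1 and 11.3.1, or say in 11.1 why 10 units per subject are credited when 150 values are analysed. Do not rely on a period effect with AR(1) residuals as the sole remedy.

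The cost is a sentence or two in the protocol and a few lines of code, with no new data. Intervals will be wider. In the most adverse heterogeneity case above, a correctly sized test would have power of about Φ(0.300/0.112 − 1.96) = Φ(0.72) ≈ 0.76 for a 1.35 ratio.
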